## Abstract

The present article describes the protocol of a mixed-methods study (an observational cohort design and focus groups), aimed to examine neuropsychological functioning and other biopsychosocial outcomes, therapeutic adherence and unmet care needs in paediatric population undergoing solid organ or allogeneic hematopoietic transplant during the pre- and post-transplant phases. Following a multi-method/multi-source approach, neuropsychological domains will be comprehensively measured with objective tests (SDMT, K-CPT 2/CPT 3, TAVECI/TAVEC, WISC-V/WAIS-IV Vocabulary and Digit Span subtests, Verbal Fluency tests, Stroop, ROCF, and TONI-4); ecological executive functioning, affective and behavioral domains, pain intensity/interference, sleep quality and therapeutic adherence will be assessed through questionnaires (parent/legal guardians-reported: BRIEF-2 and BASC-3; and self-reported: BASC-3, BPI, PROMIS, AIQ and SMAQ); and blood levels of prescribed drugs will be taken from each patient’s medical history. These outcomes will be measured at pre-transplant and at 4-weeks and 6-months post-transplant phases. The estimated sample size was 60 patients (any type of transplant, solid organ, or hematopoietic) from La Paz University Hospital (Madrid, Spain). Finally, three focus group sessions will be organized with patients, parents/guardians, and transplant clinicians (*n* = 15, with 5 participants per group), in order to qualitatively identify unmet care needs during the pre-, and post-transplant stages of the process. The study protocol was registered at ClinicalTrials.gov (NCT05441436).

## Introduction

1

Healthcare professionals and researchers focus on optimizing clinical and patient-reported transplant outcomes in children and adolescents. In doing so, studies must elucidate when the introduction of diagnostic tests and interventions, frequently very time-consuming, is more cost-effective, whether in the pre-, peri-, and/or post-transplant phases (Annema et al., 2023).

The intervention of Mental Health Liaison teams in this clinical population has been shown to be fundamental in the evaluation of the suitability of living donor candidates, assessing the recipient’s understanding of the transplant, treating psychopathological comorbid conditions, and in the intervention with the patients’ relatives (Amatya et al., 2021). Moreover, psychosocial predictors of medical regimen adherence must be monitored by Mental Health professionals throughout the whole process, both in the pre- and post-transplantation phases, to prevent negative medical outcomes (e.g., increased allograft rejection, loss of the organ, retransplantation, and death) (Killian et al., 2018). However, although these lines of intervention have been, to some extent, covered in some children hospitals, the scientific evidence accumulated to date identifies other areas of action that every reference hospital for paediatric transplantation should protocolize. In particular, these include standardized assessment of patients throughout the entire process (pre-, post-transplant and follow-up phases) on biopsychosocial (quality of life, emotional and behavioral problems) and neuropsychological domains (Jesse and Haver, 2022), which will be the main objective of this project.

In particular, the promotion and evaluation of the mental health of patients (Di Giuseppe et al., 2020; Ünay et al., 2020; Proli et al., 2021), as well as of their relatives, must be an essential axis of action in the clinical care of the paediatric population undergoing transplantation, which has become especially evident during the recent health emergency situation resulting from the COVID-19 pandemic (Zhao et al., 2020). Importantly, patients’ mental health problems (such as, anxiety, depression, distress, behavioral problems) and family conflicts are modifiable psycho-social predictors of non-adherence to medications (Killian et al., 2018) and, particularly relevant, suffering depression increases risk of mortality among patients after organ transplant (Dew et al., 2015). Moreover, family conflicts have been associated with worse evolution of the mental health of children and adolescents after transplantation (Sinatora et al., 2020). Therefore, it is essential to identify dysfunctions at the family and other interpersonal level in this population (Chardon et al., 2020).

Moreover, as mentioned previously, other functional and clinical indicators of the paediatric population in the process of transplantation or in those already transplanted should also be systematically incorporated into hospitals’ protocols for these patients, such as neuropsychological evaluations. In this regard, scientific literature confirms that this clinical population presents outstanding needs both at the level of global intellectual functioning and specific neurocognitive domains, both in transplant recipients of different solid organs (Alonso and Sorensen, 2009; Urschel et al., 2018; Gold et al., 2020; Karakizlis et al., 2022; Østensen et al., 2022) and of hematopoietic progenitors (Fahnehjelm et al., 2018; Wu et al., 2022).

Specifically, paediatric solid organ transplant recipients have demonstrated overall worse performance in attentional control, working memory, processing speed and executive functioning in general (Cushman et al., 2020). Moreover, verbal comprehension and perceptual reasoning are also found to be significantly below those of healthy children. Some studies indicate that when compared to the reference group, twice as many children in the transplant group obtain total IQ scores of less than 70 (Fredericks et al., 2014). Common risk factors for these neurocognitive difficulties include malnutrition, infections, long hospital admissions, and altered environmental interactions that reduce age-normative stimulation. Moreover, each patient subgroup (according to organ transplant type) had specific reasons for cognitive risks during the transplantation process. For example, among patients with renal disease, the accumulation of waste products from impaired renal function can affect cognitive outcomes. Similarly, liver patients could suffer cognitive consequences through the accumulation of ammonia as well as chronic malnutrition. For patients undergoing heart transplantation, there is a cognitive risk associated with cardiopulmonary bypass and circulatory arrest if they have undergone surgical repair of cardiac abnormalities, as well as an increased risk of ischemic hypoxia throughout the disease course (Reed-Knight et al., 2015).

Likewise, cognitive impairment is an established sequela of allogeneic hematopoietic transplantation. Amongst others, it has been noted that these patients have significant deficits in learning, processing speed, verbal fluency, memory, and executive functioning. There are multiple potential contributors to cognitive impairment in this clinical population, including chemotherapy cytotoxic effects, increased incidence of autoimmune phenomena, and a chronic proinflammatory state affecting brain health, even in the absence of frank Graft-Versus-Host-Disease (GVHD). This population is also more vulnerable to post-transplant infections, which can potentially affect cognitive performance (Buchbinder et al., 2018).

Although past research has demonstrated neurocognitive difficulties in paediatric patients’ post-transplantation phase, there are limited data examining patients’ cognitive functioning prior to transplantation (Reed-Knight et al., 2015). Therefore, this study proposes a comprehensive neuropsychological protocol to be implemented before and after transplantation to measure changes over time. This assessment, together with the evaluation of other biopsychosocial domains, will allow for the early detection of high-risk clinical conditions at the mental health level as well as the identification of peri-surgical neurocognitive disorders (Kaustov et al., 2021). Similarly, early identification of these deficits is essential to be able to activate potential educational adaptations or cognitive rehabilitative interventions, which will be optimally effective if implemented in the critical periods of child neurodevelopment (Karakizlis et al., 2022).

In addition, it is now strongly recommended that the planning of psychological interventions should follow a co-design approach with those involved in the care process (Palermo et al., 2021; Annema et al., 2023). In this sense, throughout this project, several focus groups will be carried out with patients and their families, as well as with their medical/surgical professionals of reference, to identify the unmet care needs throughout the pre-, peri-, and postoperative phases. These findings will allow for the design of future psychological interventions for surgical prehabilitation (i.e., to prepare the patient to be in the best possible state before surgery).

Finally, the most recent scientific evidence focuses on identifying which factors mediate the relationship between several patient-reported outcomes (e.g., pain, anxiety, depression and sleep disorders) and their adherence to prescribed treatments in the paediatric population, identifying executive functioning as a variable of special interest (Caes et al., 2021).

Despite the evidence cited above and to the best of our knowledge, no study has been conducted in Spanish paediatric populations with the aim of identifying potential neurocognitive and other biopsychosocial concerns, as well as unmet care needs throughout the entire transplantation process.

## Objectives

2

The objectives of the present study were as follows:

− Examine neuropsychological and other biopsychosocial outcomes in paediatric population during the pre- and post-transplant phases at 4 weeks and 6 months.− Identify unmet care needs of patients and their parents/guardians in the pre- and post-transplant phases.− Compare neuropsychological and other biopsychosocial outcomes by age groups and type of transplant.− Compare pre- and post-transplant therapeutic adherence by age groups and type of transplant.− Analyze the variables that mediate the relationship between several patient-reported outcomes and treatment adherence.− Identify possible peri-surgical neurocognitive disorders.

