### Hypotheses

2.1

The hypotheses of the present study are listed below and are based on clinical experience as well as on the available scientific literature (Caes et al., 2021):

*H1:* Improvements in some neuropsychological domains (e.g., processing speed and executive functioning) will be observed between the pre- and post-transplant phases.

*H2:* Improvement in some parent- (or guardians-) and patient-reported outcomes (e.g., emotional-behavioral problems and personal adjustment) will be observed between the pre- and post-transplant phases.

*H3:* Patients under cardiac and lung transplantation will suffer poorer neuropsychological outcomes and more emotional-behavioral problems, both in the pre- and post-transplantation phase, than patients under kidney transplantation.

*H4:* Patients under hematopoietic transplantation will suffer poorer neuropsychological and more emotional-behavioral problems, both in the pre- and post-transplantation phase, than patients under solid organ transplantation.

*H5:* Older patients will show poorer therapeutic adherence levels than younger patients.

*H6:* Executive functioning will mediate the relationship between several patient-reported outcomes (e.g., pain, anxiety, depression and sleep disorders) and therapeutic adherence.

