### Selection of participants

3.2

The potential participants will be all those children and adolescents already included (or in the imminent phase of being included) in the waiting list for a transplant of any solid organ (single or combined), or allogeneic hematopoietic from La Paz University Hospital (Madrid, Spain). The estimated sample size was 60 patients (for any type of transplant, organ, or hematopoietic). Recruitment will last from November 1, 2022, until June 2024.

For this purpose, a non-probabilistic technique of incidental sampling (or purposive sampling technique) will be used in this study according to the following inclusion and exclusion criteria listed below, based on other related studies:

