#### Inclusion criteria

3.2.1

Age between 6 and 18 years.Females and males.Spanish as mother tongue or a very high level of Spanish to understand their participation in the study as well as to be able to complete the measurement instruments.

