### Variables and instruments

3.4

The variables measured in this project, the instruments used and the informants who will complete each measure are detailed below:

Socio-demographic (sex, age, patient’s level of studies, parents’ level of studies) and clinical variables (current pharmacological treatment—active substance and dose). These data will be collected with an initial survey created *ad hoc* for the present study.Processing speed. The Symbol Digit Modalities Test (SDMT) (Smith, 2002) will be administered to patients.Visual sustained attention/vigilance. The Kiddie Continuous Performance Test, second edition (K-CPT 2) (Conners, 2006) will be administered to children aged 4 to 7 years, and the Continuous Performance Test, third edition (CPT 3) (Conners, 2014) to children aged 8 and above. This test computes several scores, as follows: Detectability, Omissions, Commissions, Perseverations, Hit Reaction Time (HRT), HRT Standard Deviation, Variability, HRT Block Change and HRT Inter-Stimulus Interval Change.Immediate and delayed verbal memory. A Spanish test based on the California Verbal Learning Test will be administered to patients. Specifically, the Spain-Complutense Verbal Learning Test for Children (TAVECI) (Benedet et al., 2017) will be administered to children aged 3 to 16 years; and the version for older patients (TAVEC) (Benedet and Alejandre, 2014) will be applied to adolescents aged 16 to 18 years. This test allows calculating a wide range of scores regarding the verbal memory performance, and the following scores will be specifically used in this study: Immediate Recall, Short Delay Free Recall, Short Delay Cued Recall, Long Delay Free Recall, Long Delay Cued Recall, Long Delay Recognition, Semantic clustering strategies, Serial clustering strategies, False positives, and Discriminability.Semantic memory. The Vocabulary subtest of the Wechsler Intelligence Scale for Children, fifth edition (WISC-V) (Wechsler et al., 2015) will be administered to patients up to the age of 16.11 years, and the adult version, fourth edition (WAIS-IV) (Wechsler, 2012), will be applied to patients up to 18 years.Verbal working memory and cognitive flexibility. The Digit Span subtest of the WISC-V (Wechsler et al., 2015) or the WAIS-IV version (Wechsler, 2012) will be administered to patients. Three neurocognitive domain-specific scores will be considered from the three differentiated parts of the task (Forward, Backward, and Sequencing subscales), as well as the global score (Digit Span) as a measure of cognitive flexibility (Wechsler et al., 2015).Verbal fluency. The Verbal Fluency Test (TFV) (Portellano Pérez and Martínez Arias, 2020) will be administered to patients. This test calculates the following eight scores: Phonological fluency, Semantic fluency, Excluded-letter fluency, Total Fluency Index, Errors in phonological fluency, Errors in semantic fluency, Errors in excluded-letter fluency and Total errors.Ability to inhibit cognitive interference. The Stroop Colour Word Test (SCWT) (Golden, 2020) will be administered to patients. Four scores can be computed from this test, such as: the Word reading (W), the Colour naming (C), the Colour-word (CW) and Resistance to Interference.Visuo-constructive organizational ability and immediate and delayed visual memory. The Rey-Osterrieth Complex Figure (ROCF) test (Rey, 2003) will be applied to patients. This test generates four scores: a copy score (accuracy in terms of visual–spatial constructional ability), the time required to copy the figure, and two delayed-recall scores (at 3 and 30 min).Non-verbal Intelligence. The Test of Non-verbal Intelligence, fourth edition (TONI-4) (Brown et al., 2019), using both parallel forms (A and B), will be administered to patients.Ecological Executive Functioning. The Behavior Rating Inventory of Executive Function, second edition (BRIEF-2) (Maldonado-Belmonte et al., 2017), in its parent-reported version, will be completed by the patient’s parents (or legal guardians).Emotional and behavioral problems. The Behavioral Assessment System for Children and Adolescents, third edition (BASC-3) (Reynolds and Kamphaus, 2020) will be administered, both the parent-reported version, by the patient’s parents (or legal guardians), and the self-reported version, by the patient. This questionnaire covers the personal (e.g., adaptive skills, resiliency, externalizing, and internalizing problems) and interpersonal/social domains (e.g., school problems, relationships with parents, interpersonal relations) of each patient.Pain intensity and interference. The Brief Pain Inventory (BPI) (Badia et al., 2003) will be used as a self-reported measure by patients. This questionnaire includes questions (from 0 to 10 referring to the last seven days) covering two dimensions: pain intensity (worst and mildest pain in the week, average pain, and current pain), and pain interference (general activity, mood, walking, school, sleep, as well as enjoyment of life).Sleep problems. The PROMIS Pediatric Sleep Disturbances Short Form (Forrest et al., 2018) will be used as a self-reported questionnaire by patients. It is a 4-item questionnaire that assesses problems of sleep onset and maintenance in the last 7 days.Insomnia. The Adolescent Insomnia Questionnaire (AIQ) (Bromberg et al., 2020) will be used as a self-reported measure by patients. It is a 13-item questionnaire that covers three domains: Sleep Dissatisfaction and Impairments, Sleep Onset, and Sleep Maintenance.Adherence to treatment. The Simplified Medication Adherence Questionnaire (SMAQ) (Ortega Suárez et al., 2011) will be used to evaluate therapeutic adherence as a self-reported measure. Also, blood levels of the prescribed drugs (mainly immunosuppressants) will be used to objectively evaluate therapeutic adherence, which will be extracted from the clinical history of each patient.

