### Statistical analyses

3.6

The data will be processed primarily using the statistical software IBM SPSS Statistics 29, among others, and mainly the following analyses will be performed:

First, descriptive analyses will be carried out for all variables to identify possible errors or outliers in dataset. Then, zero order correlation analyses will be computed to determine the degree of association between variables; and partial correlation analyses will be conducted to examine its association excluding the effect of other confounding variables.

Additionally, as main statistical analysis, a mixed Analysis of Covariance will be performed to evaluate the main effects between groups (2 types of transplant: solid organ and haematopoietic) and within groups (time variable with 3 levels: pre-, post-transplantation at 4-weeks and 6-months follow-up) as well as potential interactive effects, excluding the effect of confounding variables. *P*-value adjustments for multiple comparison will be performed. In turn, other analytical strategies will be used to examine time series such as latent grow models. Finally, innovative statistical analyses based on multiple linear regression will be developed to examine the relative weight of the different predictor variables on the criterion variables, already published elsewhere (Fernández-Jiménez and Arnett, 2015).

All these statistical analyses will be complemented with the appropriate effect size indexes for each statistical test (e.g., *f*, omega-square and *R^2^* indexes) (Cohen, 1992). Additionally, Reliable Change Index (RCI) will be computed in order to determine the real change of each individual score between measurements over time (Kiselica et al., 2023).

Since the main statistical analysis in this study will be a mixed Analysis of Covariance (2 × 3), with a statistical power = 0.95 and a risk/significance level of alpha = 0.05, to detect at least a moderate effect size (*f* = 0.25) on the outcome variables included, a minimum sample size of 36 patients will be required according to GPower 3.1.9.4 software.

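### The adherence objective compares by undefined age groups; testing age in years would avoid losing information on the age hypothesis (H5)

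*Protocol article*

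**What the plan says.** Two objectives in the Objectives section group by age. The third-listed is to "Compare neuropsychological and other biopsychosocial outcomes by age groups and type of transplant" and the fourth is to "Compare pre- and post-transplant therapeutic adherence by age groups and type of transplant". Neither they nor any later section say how many groups there are or where they divide.

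H5 (Hypotheses) reads: "Older patients will show poorer therapeutic adherence levels than younger patients". Age is among the items in the initial survey: "Socio-demographic (sex, age, patient’s level of studies, parents’ level of studies". The eligible range is wide: "Age between 6 and 18 years". Table 1 lists both adherence measures, the SMAQ and drug blood levels, for ages 6 to 18.

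On numbers, Selection of participants says "The estimated sample size was 60 patients", and Statistical analyses says "a minimum sample size of 36 patients will be required according to GPower 3.1.9.4 software", "with a statistical power = 0.95 and a risk/significance level of alpha = 0.05". That minimum is for the mixed analysis of covariance, whose factors are transplant type and time. The same section plans zero-order and partial correlations and multiple linear regression, but assigns age to none of its analyses. The wording of the objectives is therefore the only indication of how age is to be compared.

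**The concern.** Grouping a continuous predictor treats all children on one side of a cut as the same age. If adherence changes gradually over 6 to 18 years, that discards usable information, and a sample of 60 has little to spare. H5 can be tested without any groups.

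Undefined groups also leave the cut-points open. Table 1 alone offers several natural candidates: 8 years (change of continuous performance test, start of BASC-3 self-report), 11 years (start of the AIQ) and 16 years (change of verbal learning test). If the cut were picked after looking at the results, the nominal 5% level for H5 would no longer hold.

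**Working it through.** **The plan's own figure.** The minimum of 36 does not concern age. For the within-subject or interaction test with 2 groups and m = 3 times, the noncentrality is λ = f²·N·m/(1 − ρ). At f = 0.25, N = 36 and ρ = 0.5, λ = 0.0625 × 36 × 3/0.5 = 13.5, and power is 0.906; power 0.95 would need N = 44. N = 36 is obtained at ρ of 0.59 to 0.60. The article does not state ρ, so 36 can be neither confirmed nor refuted. No figure is given for any age comparison.

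**Information kept after grouping.** For a linear age effect, the share kept is (variance of the group means of age)/(total variance of age). The number of groups and the age distribution are assumptions.

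- Ages uniform on 6 to 18: total variance = 12²/12 = 12.
- Two equal groups: means 9 and 15, between-group variance 3² = 9, share kept 9/12 = 0.75.
- Three equal groups: means 8, 12 and 16, between-group variance (16 + 0 + 16)/3 = 10.67, share kept 0.889.
- One cut at 8 or at 16: groups of 1/6 and 5/6 with means 6 years apart, between-group variance (1/6)(5/6)(36) = 5, share kept 5/12 = 0.417.
- Normal ages, two equal groups: 2/π = 0.637.
- Normal ages, three equal groups: outer means ±1.091 SD, so (2/3)(1.091²) = 0.793.

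| Equal groups | Loss, uniform ages | Loss, normal ages |
|---|---|---|
| 2 | 25.0% | 36.3% |
| 3 | 11.1% | 20.7% |
| 4 | 6.3% | 13.9% |
| 5 | 4.0% | 10.3% |

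With 60 patients, two groups act like 60 × 0.75 = 45 or 60 × 0.637 = 38.

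**Power.** Fisher z approximation, two-sided 0.05: power = 1 − Φ(1.96 − atanh(r′)·√(N − 3)), where r′ = r·√(share kept). The correlation r is assumed, and adherence is treated as a roughly continuous score. For r = 0.35 and N = 60, √57 = 7.550:

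- Age in years: atanh(0.350) × 7.550 = 2.759, power 0.79.
- Two groups, uniform: r′ = 0.303, 0.3129 × 7.550 = 2.363, power 0.66.
- Two groups, normal: r′ = 0.279, 0.2869 × 7.550 = 2.166, power 0.58.

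| r | N | Age in years | 2 groups, uniform | 2 groups, normal |
|---|---|---|---|---|
| 0.20 | 60 | 0.33 | 0.26 | 0.23 |
| 0.30 | 60 | 0.65 | 0.52 | 0.45 |
| 0.35 | 60 | 0.79 | 0.66 | 0.58 |
| 0.40 | 60 | 0.89 | 0.78 | 0.70 |
| 0.50 | 60 | 0.99 | 0.94 | 0.89 |
| 0.35 | 36 | 0.56 | 0.44 | 0.38 |

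At N = 60 with uniform ages the drop is about 0.07 at r = 0.20, 0.13 at r = 0.35 and 0.05 at r = 0.50. The value 0.35 is therefore near the worst case.

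**Open cut-points.** Simulated null studies, uniform ages, at least 5 children per side:

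- One cut fixed in advance rejects at about 0.05.
- Reporting the best of the whole-year cuts 8 to 16 rejects at about 0.21 to 0.23 with N = 60.
- Reporting the best of 8, 11 and 16 rejects at about 0.13 with N = 60.

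**The case against.** An objective says what is compared, not how a variable is coded. Statistical analyses never splits age, and its planned correlations and regression could take age in years. The number of groups and the cuts may sit in an analysis plan that is not shown. This stands, and it makes the loss conditional. It does not remove the point: the objectives name grouping, and nothing in the article overrides it.

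A reader might infer three stronger things, none of which the document supports.

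- *That the study throws away a quarter or more of its information on age.* A quarter needs a two-way median split of evenly spread ages. Three to five equal groups lose 4% to 21%; only two groups, or badly uneven cuts, reach a quarter or more.
- *That H5 predicts a gradient which the objectives contradict.* H5 is an older-versus-younger statement and fits either a trend or a group contrast.
- *That the H5 test will have a false-positive rate above 0.20.* That presumes a search over many cuts, which no section describes.

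Linearity is also an assumption. If adherence stepped down at age 12 with ages uniform, two groups cut there would lose nothing, and a linear term would keep only 75%.

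Finally, age bands have a measurement rationale for some outcomes of the third objective. The continuous performance, verbal learning and Wechsler tests change version with age, and the BASC-3 self-report, AIQ and PROMIS forms do not cover all of 6 to 18. A single age term would then run across different tests. This limits the remedy there, but not for adherence.

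**Conclusion.** The point holds in conditional form for the adherence objective and H5. The objective compares by age groups that the article does not define, while age is recorded and both adherence measures span the full age range. With a two-way equal split and a roughly linear effect, 25% to 36% of the information on age is lost; with three equal groups, 11% to 21%. At an assumed correlation of 0.35 and 60 patients, two groups reduce power from 0.79 to 0.66 or 0.58. The inflated false-positive rate is a risk only if cuts are chosen after seeing the data.

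The split, the age distribution, the linearity and the correlation are all assumptions. The point touches one hypothesis fully and the third objective in part. It does not affect the main analysis of transplant type by time.

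**What to change.** Word the adherence objective, and the test of H5, as a comparison by age in years at the pre-transplant assessment, entered as a continuous term, with one quadratic term as a check of linearity. Keep age bands for descriptive tables, with their limits fixed in advance.

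For the third objective, use continuous age where one instrument covers 6 to 18 years (for example the SDMT, verbal fluency, Stroop, Rey figure, TONI-4 and BRIEF-2). Where the version changes with age, use age-normed scores or account for the version in the model. An age effect on normed scores then means a departure from same-age peers.

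The cost is a change of wording and one or two model terms for adherence, slightly more for the version-dependent tests. No new data are needed, and the article already plans regression and correlation. The downside is that a linear term is less efficient if the true effect is a step at one age. If the investigators expect such a step, they should state the age and the reason before the data are examined.
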